#### Research interviews

The schedule of trial procedures and assessments for participants, including the timing of research and clinical interventions is shown in Table 2. Participants are scheduled to have interviews with researchers at 3-weekly intervals during the 12-week intervention (Weeks 1, 4, 7, 10 and 13), and again 12 weeks after the intervention (Week 25). These interviews will be face-to-face with a researcher, although they can be undertaken by telehealth if required. All data collected at researcher interviews will be entered directly into an electronic database, REDCap, and kept confidential from treating clinicians. Participants will be reimbursed with shopping vouchers for time, inconvenience, and expenses of attending research interviews [59].

**Table 2 Tab2:** Schedule of trial procedures and assessments

Assessment/ Procedure	Screening	Intervention Phase					Follow-up
**Week**	**-t**_**1**_	**1**	**4**	**7**	**10**	**13**	**25**
**ENROLMENT**							
Phone screen (eligibility)	X						
Medical screen/assessment (eligibility)^a^	X						
Urine drug screen and βhcG	X						
Blood test (LFTs)	X						
Informed consent		X					
Enrol and Randomisation		X					

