**Methods/Design:**

A phase III multi-site, randomised, double-blinded, placebo controlled parallel design of a 12-week course of CBD to placebo, with follow-up at 24 weeks after enrolment.

Two hundred and fifty adults with moderate-to-severe CUD (target 20% Aboriginal), with no significant medical, psychiatric or other substance use disorders from seven drug and alcohol clinics across NSW and VIC, Australia will be enrolled.

Participants will be administered a daily dose of either 4 mL (100 mg/mL) of CBD or a placebo dispensed every 3-weeks. All participants will receive four-sessions of Cognitive Behavioural Therapy (CBT) based counselling. Primary endpoints are self-reported cannabis use days and analysis of cannabis metabolites in urine. Secondary endpoints include severity of CUD, withdrawal severity, cravings, quantity of use, motivation to stop and abstinence, medication safety, quality of life, physical/mental health, cognitive functioning, and patient treatment satisfaction. Qualitative research interviews will be conducted with Aboriginal participants to explore their perspectives on treatment.

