### Participants and recruitment

#### Eligibility criteria

The target study population is treatment-seeking adults with moderate to severe CUD under conditions of informed consent. Eligibility will be assessed by an Addiction Medicine or Psychiatry credentialed Study Medical Officer (SMO).

Inclusion criteria*:*Aged 18 to 65 years.Meeting DSM-5 criteria for moderate or severe CUD (≥ 4/11 criteria) [2], with recent frequent cannabis use (≥ 4 days per week in the preceding 4 weeks).Willing and able to provide informed consent to study procedures.Proficient in English at a conversational level sufficient to participate in a counselling intervention.

*Exclusion criteria* aim to exclude individuals with conditions that jeopardise safety or confound data interpretation:Prescribed medicinal cannabis products (e.g., CBD, THC) for any indication in the previous 4 weeks.Another active (past year) moderate-severe substance use disorder other than tobacco; determined on clinical assessment using DSM-5 criteria.Active or severe medical (e.g., pain, epilepsy, cardiovascular disease) or psychiatric (e.g., psychosis, severe affective disorder) conditions based on clinical assessment.Moderate to severe hepatic disease (transaminase elevations > 3 times, bilirubin > 2 times upper normal limits at screening).Pregnant or lactating women (based on urine β-hCG at screening).Hypersensitivity to CBD or any excipients of Investigational Product.Using medications with known drug-drug hepatic CYP-450 interactions with CBD: 3A4, (e.g., carbamazepine, fluvoxamine, methadone), 2C19 (e.g., rifampin); CYP2B6 (e.g., bupropion), CYP2C9 (e.g., warfarin).Not available during treatment or follow-up (e.g., travel, impending residential detoxification or residential rehabilitation admission, impending imprisonment).Court-mandated treatment requiring abstinence from drugs.Current active (counselling and/or medication-based) treatment for CUD.Received an investigational medicinal product within the last 4 weeks (or 5 half-lives if using long-acting investigational drugs).

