#### Recruitment, screening and assessment

Participants will be recruited from people seeking treatment at participating study sites, and/or people interested in the study in response to study advertisements at local health services, social media, and clinical trial recruitment platforms. On initial contact with the service, potential participants will be informed of the study and if interested, referred to a site coordinator to complete telephone screening. Following telephone screening, potentially eligible participants will be scheduled a face-to face assessment with a Study Medical Officer (SMO) to confirm eligibility. Potential participants will sign a medical screen consent form prior to the SMO completing a structured history, clinical examination, and any laboratory investigations with the participants. The SMO will also explain the study requirements to the potential participant and explain the study medication and any potential side effects. Eligible participants are scheduled an appointment (Week 1, Day 1) to attend for enrolment into the study. For those participants who are not eligible or choose not to participate in the study, alternative treatment options will be organised in collaboration with the patient, as clinically appropriate.

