#### Informed consent, randomisation and blinding

Written informed consent is obtained on Week 1, Day 1 of the study prior to the commencement of all subsequent study procedures. Consent is obtained with the site coordinator independent of treating clinicians, to minimise ‘pressure’ to participate in the study.

The randomisation schedule has been developed by an independent statistician, with eligible participants randomised in a 1:1 ratio between groups using variable block randomisation to help maintain blinding, with subjects stratified by (a) site (to achieve approximately equal numbers of active and placebo at each site) and (b) Indigenous Australian status (to allow direct between-group statistical comparisons within Indigenous Australian participants).

Participants, clinicians, and researchers involved in service delivery, data collection and analysis will remain blinded to study conditions using matched placebos manufactured by the same manufacturer. CBD and placebo will be packaged in identically labelled containers with the participant’s ID number and site. Aside from site trial pharmacists (who have no direct contact with participants), all other members of the clinical or research teams will be blinded to group allocation.

Unblinding will occur after all data are collected, entered, cleaned and the trial database has been locked. In circumstances where allocation needs to be unblinded (e.g. severe adverse event), the principal investigator will authorise the local site investigator to break the blind (via the site trial pharmacist).

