#### Clinical reviews

Participants will have 3-weekly medical reviews with the SMO over the 12-week intervention (Weeks 1, 4, 7, 10 and Week 13). At each appointment, the SMO will review cannabis and other substance use since the last appointment, other health and social issues, and client goals, complete Concomitant Medications and Adverse Events assessments, collect UDS, and supply medications dispensed by the trial pharmacist.

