**INTERVENTION**							
Medication [CBD or placebo] dispensed		X	X	X	X		
Adverse Events Assessments^b^			X	X	X	X	
Concomitant Medications^b^			X	X	X	X	
CBT counselling intervention^c^			X		X		

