**RESEARCH ASSESSMENTS**							
Research Interviews^d^: Collection of UDS, TLFB, Quantity of Cannabis Use, SUG, Rates of Abstinence, PROMIS-29, Testing of the Blind, CWS, MCQ, ATOP, FTND		X	X	X	X	X	X
DSM-5, PTSD, MPQ		X				X	X
TSQM, DEQ-5			X	X	X	X	X
PSIa		X		X		X	X
Treatment Retention						X	
Cognitive assessments^e^: RAVLT, NART-17, Eriksen Arrow Flankers Task, N-Back, Digit Span Task, TMT		X				X	
Interviews with Indigenous Australian participants + m-EDS^f^		X		X			

^a^Medical screening to be conducted within 4 weeks of study enrolment on Week 1, Day 1

^b^Adverse event assessments and concomitant medications are assessed by the study medical officer or clinical nurse specialist

^c^Cognitive behavioural therapy intervention to be conducted by experienced cannabis counsellors. Three sessions to be conducted over the first 6 weeks of treatment and one session between weeks 7–13 of intervention period

^d^All research interviews and cognitive assessments will be conducted by the site coordinator. See Table 1 for descriptions of each research measure

^e^RAVLT: This task assesses verbal learning and memory; NART-17 = National Adult Reading Test: this task assesses pre-morbid IQ; Eriksen Arrow Flankers Flankers: This test assesses both choice reaction time and the ability to ignore distracting but irrelevant information; N-back: this is a working memory task; Digit span task: evaluates working memory; Trail Making Test: assesses attention, processing speed, and cognitive flexibility

^f^Modified Everyday Discrimination Scale (m-EDS) will be conducted at Week 1 baseline and a qualitative research interview with consenting Indigenous Australians will be conducted by the study’s Aboriginal Research Coordinator between weeks 7–13

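### Urine β-hCG is scheduled at screening only, so no scheduled test would detect an unsuspected pregnancy on Day 1 or before the Week 4, 7 and 10 supplies

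*Protocol article*

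**What the plan says.** Two places in the protocol article fix when pregnancy is tested, and they agree. The enrolment block of Table 2 has the row "Urine drug screen and βhcG", with a single mark, under screening. The exclusion list under Eligibility criteria reads "Pregnant or lactating women (based on urine β-hCG at screening".

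Enrolment is a different appointment. Under Recruitment, screening and assessment: "Eligible participants are scheduled an appointment (Week 1, Day 1) to attend for enrolment into the study". The section on Informed consent, randomisation and blinding then states: "Written informed consent is obtained on Week 1, Day 1 of the study prior to the commencement of all subsequent study procedures". Table 2 puts randomisation at Week 1 as well.

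The abstract says that participants receive CBD "or a placebo dispensed every 3-weeks". The Table 2 row "Medication [CBD or placebo] dispensed" is marked at Weeks 1, 4, 7 and 10. The Clinical reviews section itemises what the medical officer does at Weeks 1, 4, 7, 10 and 13. The list ends with the instruction to "collect UDS, and supply medications dispensed by the trial pharmacist" and names no pregnancy test. Table 1 gives the analytes of the repeated urine drug screen (UDS) as THC-COOH and CBD-COOH; β-hCG is not among them.

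Footnote a to Table 2 reads "Medical screening to be conducted within 4 weeks of study enrolment on Week 1, Day 1". It is attached to the medical screen row, not to the β-hCG row.

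**The concern.** The article introduces its exclusions as covering conditions that endanger safety or confound interpretation, and pregnancy is one of them. A single test before a separate enrolment visit and 12 weeks of dosing can enforce that exclusion only against a pregnancy already detectable at screening. A woman whose pregnancy is very early at screening, or begins later, could be randomised, given her first supply and resupplied three times with no further scheduled test. A medical officer may still test on suspicion, and a woman known to be pregnant on Day 1 remains excluded. The gap concerns pregnancies that nobody suspects. What is at stake is participant safety, not either primary endpoint.

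**Working it through.** The plan gives no figure on this point to reproduce. The check sets the test date against the supply dates.

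**Inputs.** Supplies at Weeks 1, 4, 7 and 10 (Table 2). Treatment of 12 weeks, or 84 days (Medications). Allocation 1:1 (Informed consent, randomisation and blinding). Gap g from screening to Day 1: not stated directly for the β-hCG. The lower limit is about 0 days. The upper limit is 28 days only if footnote a also covers the β-hCG. That is an inference from Recruitment, screening and assessment, which places laboratory investigations within the medical screen.

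**Step 1: visit days.** Day = (week − 1) × 7 + 1. Weeks 1, 4, 7, 10 and 13 are Days 1, 22, 43, 64 and 85.

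**Step 2: age of the only scheduled test at each supply.** Age = g + (week − 1) × 7.

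| Supply | g about 0 | g = 28 (inferred) |
|---|---|---|
| Week 1 | 0 | 28 |
| Week 4 | 21 | 49 |
| Week 7 | 42 | 70 |
| Week 10 | 63 | 91 |

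The g = 0 column does not depend on footnote a. Even there, the three later supplies are made on a test at least 21, 42 and 63 days old. They cover 3 × 21 = 63 of 84 dosing days, and 63/84 = 75%.

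**Step 3: study-drug days that can be supplied after a pregnancy becomes detectable, by scheduled testing alone.** Under the current schedule this is every dosing day left: 84 from Day 1, 84 − 21 = 63 from Day 22, 84 − 42 = 42 from Day 43, and 84 − 63 = 21 from Day 64. With tests on Days 1, 22, 43 and 64, a pregnancy detectable by Day 1 is found before any dose. One that becomes detectable just after a test is found before the next 21-day supply.

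| Becomes detectable | Current | With repeat tests |
|---|---|---|
| Between screening and Day 1 | up to 84 | 0 |
| Just after Day 1 | up to 84 | 21 |
| Just after Day 22 | 63 | 21 |
| Just after Day 43 | 42 | 21 |
| Just after Day 64 | 21 | 21 |

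The last row shows no gain, because no later supply remains to be withheld. With 1:1 allocation about half of these days are placebo on average: 84 study-drug days correspond to 84/2 = 42 CBD days averaged over the arms.

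No expected number of pregnancies can be given, because the article states neither the number of women nor a pregnancy rate.

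**The case against.** The strongest objection is that the article condenses a full protocol that is not shown, and on-treatment pregnancy testing is the kind of operational detail that may be left there. Table 2 is also not exhaustive. It has no row for the medical reviews themselves, and Table 1 lists adverse event assessment at Week 1 where Table 2 has no mark. A missing mark is therefore weaker evidence than it looks. Moreover, the exclusion wording governs how eligibility is judged, not how women are monitored on treatment.

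Part of this stands. Support is firmest for the Day 1 test and weaker for Weeks 4, 7 and 10. It does not dispose of the point, because the article is not silent: it publishes the timing of the β-hCG twice, consistently, and itemises the later reviews without it.

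A reader might go further and infer that the trial has no other pregnancy safeguards. The article does not support that, since contraception rules and the handling of a pregnancy may be in the full protocol. Nor do Table 2 and the exclusion contradict each other.

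It is also fair to say that the article states no specific hazard of CBD in pregnancy, and that 84 days assumes nobody suspects a pregnancy through five medical reviews. The first limits the severity. The second is why the figures are given only as upper bounds.

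**Conclusion.** The point holds as a statement about the published schedule: β-hCG is fixed at screening only, and no scheduled test would find an unsuspected pregnancy that arises or becomes detectable afterwards. The upper bound is 84 study-drug days supplied after detectability, against 0 to 21 with repeat testing. This assumes that all drug is taken as supplied, that the urine test is accurate once a pregnancy is detectable, and that no one tests on suspicion.

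Two stronger readings should be resisted. The bound is not 84 days of CBD exposure to be expected, since allocation is 1:1 with placebo and clinical suspicion will often act sooner. Nor is it established that the test may be 28 days old on Day 1, because footnote a reaches the β-hCG only by inference.

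Severity is modest. It is a safety point that is worth correcting, and neither primary analysis is affected.

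**What to change.** For women of childbearing potential:

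1. Add a urine β-hCG to Table 2 at Week 1 Day 1, after consent and before randomisation and dispensing. State the order explicitly, because the article does not say whether the Week 1 review precedes randomisation. The order matters: under Participant numbers, those randomised who start no treatment are left out of the final analysis, so a positive test found after randomisation would cost a randomised participant.
2. Reword the exclusion so that it rests on urine β-hCG at screening and on Day 1.
3. Repeat the test before dispensing at Weeks 4, 7 and 10, with the result seen by the medical officer who supplies the drug. The research-interview sample should not be relied on, since those interviews may be held by telehealth and their data are kept from treating clinicians.

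A Week 13 test is optional. It falls on Day 85, after the 84 dosing days, so it could reveal exposure but not prevent it.

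The cost is a protocol amendment, with ethics review and site notification, four dipsticks per woman of childbearing potential, and an occasional late exclusion on Day 1. No new visit is needed. Whether a new sample is needed is unsettled: Clinical reviews has the medical officer collecting urine, while Tables 1 and 2 place the on-treatment UDS in the research interview. If these are one sample, a small extra aliquot would be required. If the full protocol already schedules repeat tests, the only change is to show them in Table 2.

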**INTERVENTION**							
Medication [CBD or placebo] dispensed		X	X	X	X		
Adverse Events Assessments^b^			X	X	X	X	
Concomitant Medications^b^			X	X	X	X	
CBT counselling intervention^c^			X		X		
**RESEARCH ASSESSMENTS**							
Research Interviews^d^: Collection of UDS, TLFB, Quantity of Cannabis Use, SUG, Rates of Abstinence, PROMIS-29, Testing of the Blind, CWS, MCQ, ATOP, FTND		X	X	X	X	X	X
DSM-5, PTSD, MPQ		X				X	X
TSQM, DEQ-5			X	X	X	X	X
PSIa		X		X		X	X
Treatment Retention						X	
Cognitive assessments^e^: RAVLT, NART-17, Eriksen Arrow Flankers Task, N-Back, Digit Span Task, TMT		X				X	
Interviews with Indigenous Australian participants + m-EDS^f^		X		X			

^a^Medical screening to be conducted within 4 weeks of study enrolment on Week 1, Day 1

^b^Adverse event assessments and concomitant medications are assessed by the study medical officer or clinical nurse specialist

^c^Cognitive behavioural therapy intervention to be conducted by experienced cannabis counsellors. Three sessions to be conducted over the first 6 weeks of treatment and one session between weeks 7–13 of intervention period

^d^All research interviews and cognitive assessments will be conducted by the site coordinator. See Table 1 for descriptions of each research measure

^e^RAVLT: This task assesses verbal learning and memory; NART-17 = National Adult Reading Test: this task assesses pre-morbid IQ; Eriksen Arrow Flankers Flankers: This test assesses both choice reaction time and the ability to ignore distracting but irrelevant information; N-back: this is a working memory task; Digit span task: evaluates working memory; Trail Making Test: assesses attention, processing speed, and cognitive flexibility

^f^Modified Everyday Discrimination Scale (m-EDS) will be conducted at Week 1 baseline and a qualitative research interview with consenting Indigenous Australians will be conducted by the study’s Aboriginal Research Coordinator between weeks 7–13

#### Qualitative interviews with indigenous participants

To gain insights into the experience of Indigenous Australian participants, semi-structured in-depth interviews will be conducted by Aboriginal researchers (part of the study team) at around week seven with Indigenous participants in both control and interventions groups until data saturation occurs—estimated at 15 to 25 participants. These interviews will examine topics such as (a) how participants perceived their cannabis use and identified their treatment goals, and how participants are supported by their family and community; (b) how participants engage with the study treatment procedures (medication and counselling) providing insights into future implementation. The interviews will take approximately 40 to 60 min and be digitally recorded and transcribed. A yarning methodology will be used for the data collection and analysis [60].

### Data management and monitoring

Confidentiality of participant data will be secured by removing all identifiable data and replacing it with a unique identifier. The principal investigator and coordinating researcher will have access to key files that link the unique identifier to identifiable data if unblinding is necessary.

Trial data will be electronically entered and stored on REDCap on the research drive of the University of Sydney, with regular data back-up. After the trial, the data will be stored for a minimum of 15 years in a secured study-specific folder on the research drive of the University of Sydney, and access to de-identified data will be considered upon request by the principal investigator.

An independent Data Safety and Monitoring Committee (IDSMC), comprising of an addiction medicine specialist, a statistician and clinical pharmacologist will oversee the safety monitoring of the trial, involving ongoing reviews of any adverse events arising from the administration of CBD (unblinded data). The committee will also monitor aspects of study integrity and design should any protocol changes need to be made.

### Data analysis

All data analysis will be performed using Bayesian models instead of frequentist. Bayesian methods can quantify evidence for both effects and the absence of effects, are less prone to non-convergence (due to regularisation), and sample from a joint posterior distribution, hence no family- or experiment-wise correction of regression coefficients for multiple comparisons is necessary [61]. We will use a modified intention-to-treat approach for data analysis, with group membership fixed as the medication type (placebo vs CBD) participants receive on their first study day. Missing data will be imputed via hierarchical multiple imputation [62].

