### What are suitable primary endpoints for clinical trials of CUD treatment?

A challenge in embarking on clinical trials for substance use disorder is choosing a primary endpoint. Whilst historically abstinence (cessation of all use) has often been used in cannabis treatment research, there is increasing recognition that abstinence may not be the primary goal of treatment for patients who use cannabis. A recent consensus expert panel identified suitable outcomes when undertaking clinical trials for the treatment of CUD [50], recommending primary outcomes of (a) self-reported frequency of use, using the Time Line Follow Back (TLFB) method [51]; (b) biological assessment of cannabis use, with urinalysis of the metabolite THC-COOH or oral fluid detection of THC; and (c) severity of CUD, using a structured instrument measuring DSM-5 Criteria (e.g. Mini-International Neuropsychiatric Interview (MINI) [52]). In line with these recommendations, and consistent with the previous Phase 2a RCT, we propose to use two primary endpoints to measure illicit cannabis use: (1) self-reported ‘cannabis-free days’ and (2) urinary THC-COOH, across the 12-week treatment period of the study, alongside a range of secondary outcome measures.

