## Methods

### Research hypothesis and study aims

The *research hypothesis* is that CBD, compared to placebo, will achieve statistically and clinically significant reductions in cannabis use, as measured by the number of self-reported cannabis-free days and urinary THC-COOH levels, among treatment-seeking patients with moderate-severe CUD.

The *primary aim* of the CBD-CUD study is to examine the efficacy of CBD, compared to placebo, in reducing cannabis use (as measured by self-report and quantitative measures of cannabis metabolites (THC-COOH) in urine drug screens) during treatment (Weeks 1–12) in participants seeking treatment for moderate-severe CUD, when used in combination with psychological interventions.

*Secondary aims* include examination of (i) safety, (ii) other cannabis related measures (e.g., cannabis withdrawal and cravings, cannabis-related problems); (iii) tobacco and other substance use; (iv) health and quality of life (QoL) measures, (v) patient experience measures; (vi) treatment retention rates; (vii) cognitive performance; (viii) post-treatment (Week 24) cannabis use, health outcomes and QoL measures.

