#### Participant numbers

Sample size calculations are based on the analysis of the primary outcome, that is, the difference between placebo and CBD groups in total number of Cannabis-free Days over the 12-week intervention period. Ferguson has suggested that the minimum effect size (Cohen’s *d*) for an effect of practical clinical significance is 0.4167 [55]. To achieve 90% power (two-tailed) and α = 0.05, a total of *N* = 250 (*n* = 125 per group) participants are needed to detect a between-group effect size of *d* = 0.41. Of the target 250 sample, it is estimated approximately 20% (*n* = 50) of the study sample (*N* = 250) will be Indigenous Australians.

Participants who discontinue study procedures after commencing study interventions (medication dispensed on Day 1) will not be replaced in the study but will be included in the modified intention-to-treat analyses. Participants enrolled and randomised, but do not commence any treatment (no medication dispensed or other clinical interventions) will not be included in the final analysis.

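### The joint-posterior argument does not justify waiving multiplicity across two separately modelled primary endpoints, and the stated 5% alpha and 90% power both hold only if cannabis-free days alone decides

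*Protocol article*

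**What the plan says.** Four parts of the protocol article bear on this.

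- **Endpoints.** The introduction, under the heading on suitable primary endpoints, says "we propose to use two primary endpoints to measure illicit cannabis use". Outcome measures lists the same two: cannabis-free days and creatinine-adjusted urinary THC-COOH. The hypothesis, under Research hypothesis and study aims, concerns reduced cannabis use "as measured by the number of self-reported cannabis-free days and urinary THC-COOH levels".
- **Sample size.** Participant numbers speaks of one outcome: "Sample size calculations are based on the analysis of the primary outcome, that is, the difference between placebo and CBD groups" in cannabis-free days. The criteria are frequentist: "To achieve 90% power (two-tailed) and α = 0.05", "a total of *N* = 250 (*n* = 125 per group", and these "participants are needed to detect a between-group effect size of *d* = 0.41".
- **Multiplicity.** Data analysis makes every analysis Bayesian and gives as one advantage that the methods "sample from a joint posterior distribution, hence no family- or experiment-wise correction of regression coefficients for multiple comparisons is necessary".
- **Models.** Data analysis, Primary outcomes, gives cannabis-free days a single-level regression on group and covariates. THC-COOH gets a separate mixed model with group, time, their interaction and a participant-level random effect.

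**The concern.** The waiver draws a conclusion that its premise does not carry. A joint posterior exists for the parameters of one fitted model. The two primary endpoints sit in two models, so no posterior distribution contains both treatment effects. Within a single model, too, drawing the coefficients jointly only describes their uncertainty together. It does not limit the chance that at least one looks like an effect when none is real. That takes either shrinkage through a hierarchical prior across the treatment effects or a criterion defined on the effects jointly. The article describes neither. Its hierarchical elements concern imputation and repeated measures within participants, and it credits regularisation with better convergence, not with error control.

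The sample size adds a second difficulty. Alpha and power are stated for one endpoint, while the trial has two. If the self-report and urine results disagree, the text lets either be put forward as the primary result, and the stated operating characteristics may not belong to the claim that is made.

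**Working it through.** **Inputs from Participant numbers:** two-sided alpha 0.05, power 90%, d = 0.41, 125 per arm, cannabis-free days only.

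**Assumptions, because the article gives no figure:** each endpoint is judged by whether a 95% interval excludes zero under weak priors, so that the criterion behaves like a two-sided 0.05 test; the effect on THC-COOH is also d = 0.41; the correlation r between the two test statistics lies between 0 and 0.9.

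**Step 1: reproduce the plan's figure.**

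n per arm = 2 × (1.96 + 1.2816)² / 0.41² = 2 × 10.51 / 0.1681 ≈ 125.0, which rounds up to 126 (252 in total against the stated 250).

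Power at 125 per arm: the expected test statistic is 0.41 / √(2/125) = 3.241, and Φ(3.241 − 1.96) = Φ(1.281) = 90.0% (89.8% with the exact t-test). The stated figure is right for cannabis-free days alone.

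**Step 2: two endpoints.** Let Z1 and Z2 be bivariate normal with correlation r.

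- *Either suffices*, two-sided error: 1 − P(|Z1| < 1.96 and |Z2| < 1.96). At r = 0 this is 1 − 0.95² = 9.75%.
- *Either suffices*, false claim of benefit: 1 − P(Z1 < 1.96 and Z2 < 1.96). At r = 0 this is 1 − 0.975² = 4.94%, against 2.5% for one endpoint.
- *Both required*, power: P(Z1 > 1.96 and Z2 > 1.96), each with mean 3.241. At r = 0 this is 0.90² = 81%.

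| r | Either: two-sided error | Either: error in benefit direction | Either: power | Both: power |
|---|---|---|---|---|
| 0 | 9.75% | 4.9% | 99.0% | 81.0% |
| 0.3 | 9.5% | 4.8% | 97.8% | 82.2% |
| 0.5 | 9.1% | 4.5% | 96.8% | 83.2% |
| 0.7 | 8.4% | 4.2% | 95.3% | 84.7% |
| 0.9 | 7.0% | 3.5% | 93.1% | 86.9% |

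When both are required, the error stays at or below 5%, because a false claim must also pass on the endpoint that has no effect.

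**Step 3: size needed for 90% power on both endpoints.** About 154 per arm at r = 0, 149 at r = 0.5 and 138 at r = 0.9, that is 308, 298 and 276 in total against 250.

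**The case against.** Declining familywise correction is a recognised position in a Bayesian analysis. The waiver speaks of regression coefficients, which belong to a single model, and it cites a source that is not at hand. It never says in so many words that the two endpoints share a posterior. The hypothesis joins the endpoints with *and*, and Outcome measures treats them as two measures of one construct, so the natural reading may be that both should improve. On that reading the type I error is not inflated. The hypothesis is also directional, so the relevant error under an either-suffices rule is 3.5% to 4.9% against 2.5%, about half the two-sided figure in absolute terms.

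Much of this is fair. What remains is that the sentence explicitly reaches experiment-wise correction, which goes beyond one model, and rests this on joint sampling alone. If both endpoints are required, the stated 90% is too high for the joint claim.

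Three stronger readings are tempting, and the documents do not support them.

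- A reader might infer that neither the 5% nor the 90% applies. No single rule breaks both. If either suffices, the error rises but power is above plan. If both are required, power falls but the error holds. If cannabis-free days alone decides, both figures stand.
- A reader might count the absence of a success rule or posterior threshold as an error. The article condenses a fuller protocol, and the SAP is not shown and may contain them.
- A reader might add the group-by-time terms of the THC-COOH model as further chances of success. No section proposes such a rule, so no error rate is attached to it here.

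**Conclusion.** The point holds in two parts. The reason given for waiving multiplicity is unsound, because the primary endpoints are modelled separately and joint sampling alone does not control false claims. And alpha 0.05 with 90% power was derived for one of two named primary endpoints; both figures hold only if that endpoint alone decides.

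On either two-primary reading, one figure moves: the two-sided error to about 7.0% to 9.75%, or the power to about 81% to 87%. These sizes rest on 95% intervals, weak priors, equal effects of d = 0.41 and a correlation of 0 to 0.9. Stronger priors would change them. A smaller effect on THC-COOH would pull the power for both below this range.

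**What to change.** Delete the joint-posterior justification. Then, before unblinding (which the article places after database lock), tie the stated alpha and power to one claim, in one of two ways.

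- **Fixed sequence.** Test cannabis-free days first, since the sample size uses it, and interpret THC-COOH as confirmatory only if the first test succeeds, on one named group contrast. The 5% and 90% then stand as written, provided that the Bayesian criterion matches a two-sided 0.05 test. The downside is that THC-COOH alone cannot carry the claim.
- **Co-primary, both required.** Keep both endpoints on an equal footing, say that both must succeed, and restate the power as about 81% to 87% with the assumed THC-COOH effect and correlation given. This stays closest to the two-endpoint rationale in the introduction.

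Neither option needs more participants, unless the sponsor wants to restore 90% for the joint claim. Either is a change to the stated inferential rule of a registered trial, so it should be made as a dated amendment and carried consistently through the hypothesis, the sample size and the analysis sections.
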